### Randomisation and blinding

Randomisation will be performed as follows. Based on different study centres (two groups), the patients will be classified into four groups: P group (single administration of propofol), P + S group (administration of propofol and sufentanil in combination), P + K group (administration of propofol and esketamine in combination), and P + L group (administration of propofol and lidocaine in combination) (*N* = 100 per group). The random sequence generator of the STATA MP 14 software generated random numbers and divided them into four groups. Only the nurse (A) who is responsible for preparing the trial drug knows the grouping information automatically generated by a computer. She (A) will generate the allocation sequence. The chief anaesthesiologist (B) will enrol patients and assign participants to interventions. Computer-generated random grouping numbers will be printed and placed in separate sealed envelopes. After meeting a participant who meets the inclusion criteria, the anaesthesiologist will assign the newly recruited participant to a group according to the number provided in the envelope. Both the anaesthesiologists and patients are unaware of the treatment plan. Anaesthetic drugs will be prepared and labelled with numbers by nurses and injected by the anaesthesiologists. The anaesthesiologists will record the physiological characteristics of each patient. In emergencies, the nurses can provide the anaesthesiologists the information of drugs to ensure clinical safety. The designed blinding method is as follows: This study will use the three-blind method to ensure the objective evaluation of results. The preoperative preparation of anaesthetic drugs, anaesthesia implementation for upper GI endoscopy, and PACU (postanaesthesia care unit) clinical data collection and follow-up after the operation will be performed by three medical personnel to ensure that pharmaceutist, operators, recorders, and the patients are blind to group classification. On the day of study, an envelope with the smallest sequential number was opened first and the solutions of medicines were prepared in a syringe by an investigator based on the number appeared on the paper slip. Then, the unlabelled syringes of solutions were handed over to an anaesthesiologist who was performing general anaesthesia and administrating the medicines but was blind to the contents inside of the syringes. Another anaesthesiologist who observed and recorded the data intraoperatively and postoperatively was also blinded to the medication patient had received. All sedation procedures were standardised and performed by the same anaesthesiologist who was blind to the patient groups. PACU (postanaesthesia care unit) clinical data collection and follow-up after the operation were also blinded to the therapeutic regimen. The allocation sequence was not available to any member of the research team until databases had been completed and locked. An agreement from PI will allow unblinding of individual participants on a need-to-know basis and, if necessary, termination of treatment in the event the MSO and investigator determine the participant has had a serious adverse reaction to the study medication. Emergency unblinding can be performed at any time if it is considered necessary by the principal investigator. Participants are issued with “In case of emergency” cards to be carried at all times during the study including an emergency phone number. If the trial or a single subject is prematurely unblinded, the principal investigator will document the reason for unblinding and notify the ethics committee. Unblinding of the project statistician who will analyse the data will occur at the end of the study, after the last participant has been evaluated, all data have been entered and cleaned, and the database has been locked.

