### Endpoints

The primary endpoints include the frequency of tussis, nausea and vomiting, and/or body movements observed at the insertion of the endoscope into the pharyngeal cavity or within 5 min of endoscope insertion. Secondary endpoints are as follows: (1) the time of the addition of the first drug, from the end of induction to the addition of the first drug (from the injection of the study medication to the disappearance of eyelash reflex); (2) the time of recovery from anaesthesia, from the end of the operation till the patient left the recovery room (the end of operation to consciousness return); (3) perioperative propofol doses; (4) incidence of perioperative adverse events, including tachycardia, oxygen desaturation (the time of 90% ≤ SpO_2_ < 95% for more than 10 s), breathing inhibition (the time of SpO_2_ < 95% for more than 15 s), bradycardia (< 50 beats per minute or a decrease in HR of 20% or more from baseline), and high and low blood pressure (blood pressure < 30% of the basal blood pressure or systolic blood pressure or blood pressure > 30% of the basal blood pressure); (5) incidence of postoperative adverse events (within 6 months after the operation) including nausea, vomiting, increased secretion, dizziness, over sedation, infection, nightmare, uneasiness, itching, disorientation, insanity, breathing inhibition, diplopia, diarrhoea, intestinal obstruction, urinary retention, gastroesophageal reflux, constipation, shiver, and hallucination; (6) MMSE scores, MET scores, and sleep condition after 0.5 h, 2 h, 4 h, 1 day, 2 days, 3 days, 1 week, 1 month, and 6 months of the operation; (7) pharmacoeconomic outcomes (calculated incremental cost-effectiveness ratio based on cost-effectiveness analyses).

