### Statistical methodology

Efficacy assessment is based on the intention-to-treat (ITT) population, which is defined as all randomised patients. Safety analyses will be performed in a safety evaluation set, which is a subset of all the patients exposed to a minimum of one dose of the studied medication. The SPSS 24.0 software will be used for statistical analyses. Significance will be analysed using two-sided tests, and *p* < 0.05 will be judged as the statistical significance standard. The normally distributed measurement data are presented as mean ± standard deviation (*x* ± *s*). The quartile method will be used to explain the measurement data with non-normal distribution. The repeated analysis of variance and Turkey test will be used for comparisons within a group and between multiple groups, respectively. Count data will be analysed using non-parametric tests, such as Rank-sum test, chi square test, and Fisher exact test. The multivariate regression analysis will be employed to explore the effects of different analgesic drugs combined with propofol on tussis during upper GI endoscopy. We will consider performing predefined subgroup analyses on the primary endpoints according to age, operation types, and special populations. Missing data will not be imputed. In addition, the primary endpoint analysis will also be conducted in a per-protocol set and compared with the ITT analysis to analyse sensitivity. No interim analyses are planned.

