### Sample size calculation

Based on the results of previous pretest, we speculated that compared with only propofol, the combination of small doses of esketamine with propofol could exhibit significant effect against tussis reduction incidence by a minimum of 15% during upper GI endoscopy. The type I error probability, power of test, and sample size ratio will be set to 0.05, 0.8, and 1:1, respectively. According to relevant literature reports, some believe that a sample size of 18 patients per group will provide 80% of the ability to detect differences between groups 15% difference at a level of *α* = 0.05. At *α* = 0.05, based on the 80% power difference of 15% difference in propofol demand between the levels and detection groups, the power was increased 90%, and the value [200 (109) vs.128 (53)] was added to the sample size calculation formula (*n* = 2*[(*α* + *β*) *σ*/*δ*]^2). The sample size will be estimated by considering a sample loss rate of 10%. Then, the sample size was obtained.

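### The efficacy analysis is labelled intention-to-treat in all randomised patients, but with no imputation it is a complete-case analysis, and the per-protocol set cannot test whether that matters

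*Protocol article*

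**What the plan says.** Three statements in the Statistical methodology section of the protocol article bear on this point.

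- Population: "Efficacy assessment is based on the intention-to-treat (ITT) population, which is defined as all randomised patients".
- Missing values: "Missing data will not be imputed". No exception is made for the primary endpoint.
- Sensitivity: "the primary endpoint analysis will also be conducted in a per-protocol set and compared with the ITT analysis to analyse sensitivity". No other sensitivity analysis is named.

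The same section gives the tests for counts: "Count data will be analysed using non-parametric tests, such as Rank-sum test, chi square test, and Fisher exact test". It adds a multivariate regression for the effect on tussis.

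The Endpoints section defines the primary outcome as tussis, nausea and vomiting, and/or body movement "observed at the insertion of the endoscope into the pharyngeal cavity or within 5 min of endoscope insertion".

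The Sample size calculation section closes with a general allowance: "The sample size will be estimated by considering a sample loss rate of 10" per cent. It does not say which outcome that loss refers to. The Data handling section says only that data managers will look at missing data. No section says how a randomised patient without an observed primary outcome is counted.

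**The concern.** The stated population and the stated missing-data rule cannot both hold once a single primary outcome is missing. A patient who withdraws, cancels or is not scoped after randomisation has no value for an endpoint tied to insertion. With no imputation and no counting rule, that patient is in the defined population but not in the test.

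The label matters because readers take an intention-to-treat result as protected by randomisation. A complete-case result has that protection only if the missing outcomes are unrelated to arm and prognosis, and the plan includes no analysis that probes this. The one check it names starts from the same observed patients and removes more of them. Agreement between the two could be reported as robustness when it carries no information on missing outcomes.

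**Working it through.** The plan gives no figure of its own on this point, so there is none to reproduce. The check has a textual part and an arithmetical part.

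**Which patients can be analysed**

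1. The efficacy population is everyone randomised, 100 per group.
2. The endpoint is observed at insertion or in the following 5 minutes. Without insertion there is no observation.
3. Chi-square, Fisher, rank-sum and regression analyses each need an observed outcome for every patient included.
4. Keeping an uninserted patient in the denominator as a non-event, or counting the patient as an event, assigns a value. That is single imputation, which the plan excludes.
5. The patients analysed are therefore those with an observed outcome, a complete-case set. The per-protocol set is also confined to observed outcomes, so it omits the same patients.

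**How much it could matter**

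Inputs:
- 100 randomised per group (article).
- A 15-point difference among observed patients. This is an assumption: the Sample size calculation section speaks of a reduction of at least 15% without saying whether it is absolute or relative, and gives no control rate.
- A per-arm loss *m*, equal in both arms. This is also an assumption, because the article gives none for this endpoint.

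Let *d* be the observed difference, control minus treated. In all randomised patients the extremes are:

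- every missing treated patient an event and no missing control patient: (1 − *m*)*d* − *m*
- every missing control patient an event and no missing treated patient: (1 − *m*)*d* + *m*

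The width is 2*m*, whatever the control rate.

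| Loss per arm | (1 − *m*) × 15 | Lowest | Highest | Width |
|---|---|---|---|---|
| 2% | 14.7 | 12.7 | 16.7 | 4 points |
| 5% | 14.25 | 9.25 | 19.25 | 10 points |
| 10% | 13.5 | 3.5 | 23.5 | 20 points |

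**The same in whole patients, at the 10% end only**

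Take 10 of 100 missing per group and an assumed control rate of 30%. The tests are Pearson chi-square, two-sided, without continuity correction.

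| How the missing are counted | Control | Treated | Difference | p |
|---|---|---|---|---|
| Left out (complete-case) | 27/90 | 14/90 | 14.4 points | 0.021 |
| Event in both arms | 37/100 | 24/100 | 13 points | 0.046 |
| Event in treated arm only | 27/100 | 24/100 | 3 points | 0.63 |
| Event in control arm only | 37/100 | 14/100 | 23 points | <0.001 |

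For assumed control rates from 20% to 50% the pattern is the same:
- complete-case: 14 to 16 points (p = 0.004 to 0.035)
- event in both arms: 13 to 14 points (p = 0.025 to 0.048)
- event in treated arm only: 3 to 4 points (p = 0.55 to 0.63)
- event in control arm only: 23 to 24 points (p < 0.001)

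These are bounds under an upper scenario for the loss, not forecasts.

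**The case against.** **Missingness is probably low.** The endpoint is complete within minutes of insertion in a single session. A reader might infer that the plan expects 10% of primary outcomes to be missing. The article does not support that. The 10% is a general allowance placed after a calculation on propofol demand, and follow-up runs to 6 months, so it may equally reflect later loss. This objection stands, and the 10% rows above are an upper scenario.

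**The bounds are extreme.** They need every missing patient to be an event in one arm and none in the other. This also stands: the range shows what cannot be excluded, not what is likely.

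**The direction of bias is not shown.** A reader might infer that leaving patients out favours whichever arm causes the losses. That would need the lost patients to have had more events than those who stayed. The article gives no ground for this, and a patient lost because of deep sedation might have coughed or moved less. The Assessments section does describe removing the endoscope at low saturation, but that happens after insertion, when reactions at insertion have already been seen.

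**Allocation timing.** A reader might also see two moments of allocation in the Randomisation and blinding section: "After meeting a participant who meets the inclusion criteria, the anaesthesiologist will assign the newly recruited participant to a group" and "On the day of study, an envelope with the smallest sequential number was opened first". The first sentence gives no time or place, and both can describe one event on the study day. They do not show avoidable losses between clinic and endoscopy.

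**Detail for the analysis plan.** Tipping-point methods are commonly left to a statistical analysis plan, and none is shown. But the article does not leave this matter open. It fixes the population, the no-imputation rule and the robustness check, and those three do not fit together.

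**The per-protocol comparison has a use.** It does address protocol deviations. It cannot address missing outcomes.

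**Conclusion.** The point holds as a mismatch between the stated population and the stated missing-data rule, with a robustness check that cannot detect its effect. The article does not literally say that unobserved patients leave the analysis, but this follows necessarily from its own rules and methods.

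The size is conditional. The extreme-case range for the risk difference is twice the per-arm loss, about 4 points at 2% and 20 points at 10%, to be set against a 15-point target if that target is absolute. At low loss the conclusion would hardly move. Near 10% it could change from clearly significant to not significant. The loss rate for this endpoint is not stated and is probably below 10%. The 15-point difference, the control rates and equal loss in both arms are assumptions. Nothing in the article fixes the direction of any bias. The point is therefore worth correcting because the correction is cheap, but it does not show that the primary result will be wrong.

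**What to change.** 1. Keep the no-imputation analysis, but describe it as complete-case (patients with an observed primary outcome) rather than as an analysis of all randomised patients.
2. Add one sensitivity analysis in all randomised patients that counts missing primary outcomes as event or as non-event by arm, either as best and worst cases or as a tipping point. Judge robustness to missing outcomes from this analysis. Keep the per-protocol set for the question of protocol deviations.
3. Report, by arm, how many randomised patients had no endoscope inserted, and why.

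The cost is a change of wording, one additional analysis and the recording of one item per patient. The primary test does not change. The one drawback is a wider stated uncertainty if losses turn out not to be trivial.

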### Sample size calculation

Based on the results of previous pretest, we speculated that compared with only propofol, the combination of small doses of esketamine with propofol could exhibit significant effect against tussis reduction incidence by a minimum of 15% during upper GI endoscopy. The type I error probability, power of test, and sample size ratio will be set to 0.05, 0.8, and 1:1, respectively. According to relevant literature reports, some believe that a sample size of 18 patients per group will provide 80% of the ability to detect differences between groups 15% difference at a level of *α* = 0.05. At *α* = 0.05, based on the 80% power difference of 15% difference in propofol demand between the levels and detection groups, the power was increased 90%, and the value [200 (109) vs.128 (53)] was added to the sample size calculation formula (*n* = 2*[(*α* + *β*) *σ*/*δ*]^2). The sample size will be estimated by considering a sample loss rate of 10%. Then, the sample size was obtained.

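### The sample size calculation uses propofol demand rather than tussis and does not reproduce 100 per group, so the stated power is unsupported for the primary question

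*Protocol article*

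**What the plan says.** The Sample size calculation section of the protocol article starts from the clinical aim. From a pretest, esketamine with propofol, compared with propofol alone, "could exhibit significant effect against tussis reduction incidence by a minimum of 15% during upper GI endoscopy". It then fixes the design values: "The type I error probability, power of test, and sample size ratio will be set to 0.05, 0.8, and 1:1, respectively". The Statistical methodology section adds the sidedness: "Significance will be analysed using two-sided tests".

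Next it reports a literature figure, "a sample size of 18 patients per group will provide 80% of the ability to detect differences between groups 15% difference", and moves to propofol: "based on the 80% power difference of 15% difference in propofol demand between the levels and detection groups, the power was increased 90" per cent. Here "the value [200 (109) vs.128 (53)] was added to the sample size calculation formula", which is a two-means formula, n = 2[(α + β)σ/δ]². Finally, "The sample size will be estimated by considering a sample loss rate of 10" per cent. The section ends without printing the resulting number.

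Elsewhere (Abstract, Randomisation and blinding, Intervention, Discussion) the size is 100 per group, 400 in all. The Endpoints section makes the frequency of tussis, nausea and vomiting, and/or body movements primary, and lists perioperative propofol dose as secondary endpoint (3).

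**The concern.** A sample size justification should carry the primary endpoint's effect size through to the planned number. Here the effect named first (tussis, a proportion) never enters a formula, and the quantities that do enter describe a different endpoint of a different data type. If they also fail to give the planned 100 per group, neither the number nor the power has a traceable basis.

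This matters most if the trial finds no significant difference in tussis. Someone relying on the printed 80% or 90% would take such a result as good evidence against a 15% effect, and the section gives no ground for that.

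**Working it through.** **Inputs.** Two-sided α = 0.05 (Statistical methodology). Power 0.80 or 0.90, loss 10%, and 200 (109) vs 128 (53) (Sample size calculation). The last item has no label or unit; reading it as mean (SD) is an assumption. α and β in the formula are read as their normal quantiles, 1.96 and 0.8416 (80%) or 1.2816 (90%).

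**Step 1: can the planned 100 be reproduced?**
- δ = 200 − 128 = 72.
- Root-mean-square SD: √[(109² + 53²)/2] = 85.7.
- 90% power: n = 2[(1.96 + 1.2816) × 85.7/72]² = 29.8, so 30. Loss: 29.8/0.9 = 33.1, or 34 if 30 is inflated and rounded up.
- 80% power: n = 2[(1.96 + 0.8416) × 85.7/72]² = 22.2, so 23; 26 after loss.
- Larger SD (109), 90% power: n = 48.2, so 49; 55 after loss.

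None is close to 100. With 100 per group, power for 200 vs 128 is above 99%.

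**Step 2: is the difference entered 15%?**
- 72/200 = 36%.
- A true 15% of 200 is δ = 30. With SD 85.7: n = 2[(1.96 + 0.8416) × 85.7/30]² = 128.1, so 129 at 80% power; 171.5, so 172 at 90%, both before loss.

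So the printed difference falls well short of 100 and the stated 15% overshoots it. Values near 100 do appear for δ = 30 with a one-sided test at 80% power (101 before loss with SD 85.7; 102 after loss with the plain mean SD of 81). Those contradict the two-sided test, the rise to 90% and the difference actually entered.

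**Step 3: what would 100 per group deliver for the primary question?** The protocol gives no control rate, so the rates here are assumptions. With p̄ = (p₁ + p₂)/2 and no continuity correction:

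power = Φ{[|p₁ − p₂|√n − 1.96√(2p̄(1 − p̄))] / √[p₁(1 − p₁) + p₂(1 − p₂)]}

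For a 15-point absolute fall, P + K vs P:

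| Propofol alone → P + K | 90 evaluable per group | 100 per group |
|---|---|---|
| 20% → 5% | 0.87 | 0.90 |
| 25% → 10% | 0.76 | 0.80 |
| 30% → 15% | 0.68 | 0.72 |
| 50% → 35% | 0.53 | 0.57 |
| 90% → 75% | 0.76 | 0.80 |
| 95% → 80% | 0.87 | 0.90 |

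Worked row, 25% → 10%, n = 100: p̄ = 0.175; numerator 0.15 × 10 − 1.96 × √0.28875 = 1.5 − 1.053 = 0.447; denominator √(0.1875 + 0.09) = 0.527; Φ(0.848) = 0.80.

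If 15% is a relative reduction, power with 100 per group is about 0.08 at a control rate of 20%, 0.18 at 50%, 0.34 at 70% and 0.73 at 90%.

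**The case against.** The strongest reply is that 100 per group may be adequate for tussis, with only the write-up at fault. Tussis is named as the premise, and the opening inputs fit the planned size at one plausible rate: a fall from 23% to 8% needs 90.2 per group at 80% power, and 90.2/0.9 = 100.2 after loss. That rate is not printed, so it cannot be confirmed, but it is a fair reason not to call the trial underpowered. A reader might infer underpowering from the lower rows of the table; the document does not support this, because those rows rest on assumed control rates. Nor can one say that adequate power requires a low control rate. Power is symmetric and recovers at high rates, which cannot be ruled out when the endpoint also counts nausea and vomiting and body movements.

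A reader might also want to test the 18-per-group figure against 200 (109) vs 128 (53). That is not sound: the figure is attributed to the literature, and its own sentence gives neither endpoint nor SD. Likewise, α and β printed in the formula in place of their quantiles are a matter of notation.

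The two power values are partly explained by the text, which says power was raised. Which value applies to the final size, and to which endpoint, remains unclear.

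None of this supplies a calculation for the primary endpoint or recovers 100 from the numbers printed.

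**Conclusion.** The point stands in this form: the printed calculation concerns a secondary endpoint, and under the stated two-sided test it gives about 30 per group at 90% power (33–34 after loss), at most about 49 (55) with the larger SD, against a planned 100. It also labels a 36% difference as 15% and leaves the final power unclear.

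The 80% or 90% power is therefore unsupported for the primary question, but not refuted. For a 15-point absolute fall, true power with 90 evaluable patients per group could lie anywhere from about 0.53 to 0.87 over the control rates tabulated. If 15% is relative it would be far lower at most rates. These conclusions rest on reading 200 (109) vs 128 (53) as mean (SD) and, for the power figures, on assumed control rates. The failure to reproduce 100 does not depend on any control rate.

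**What to change.** Keep N = 400 and rewrite the section:

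1. Delete the propofol-demand and 18-per-group text. Replace it with a two-proportion calculation for P + K vs P on the primary endpoint: tussis incidence, and the composite of tussis, nausea and vomiting, and/or body movements if that is the primary endpoint.
2. State the control rate seen in the pretest, whether 15% is absolute or relative, two-sided α = 0.05, and a single power value.
3. Report the power that 100 randomised and 90 evaluable per group deliver across plausible control rates.
4. Say that the comparisons of P + K with P + S and with P + L are not covered by this power statement.

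The cost is protocol wording only, with no extra patients. The downside is that the stated power may become less favourable.
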